## Abstract

**Background:**

Malaria and malnutrition represent major public health concerns worldwide especially in Sub-Sahara Africa. Despite implementation of seasonal malaria chemoprophylaxis (SMC), an intervention aimed at reducing malaria incidence among children aged 3–59 months, the burden of malaria and associated mortality among children below age 5 years remains high in Burkina Faso. Malnutrition, in particular micronutrient deficiency, appears to be one of the potential factors that can negatively affect the effectiveness of SMC. Treating micronutrient deficiencies is known to reduce the incidence of malaria in highly prevalent malaria zone such as rural settings. Therefore, we hypothesized that a combined strategy of SMC together with a daily oral nutrients supplement will enhance the immune response and decrease the incidence of malaria and malnutrition among children under SMC coverage.

**Methods:**

Children (6–59 months) under SMC coverage receiving vitamin A supplementation will be randomly assigned to one of the three study arms (a) SMC + vitamin A alone, (b) SMC + vitamin A + zinc, or (c) SMC + vitamin A + Plumpy’Doz™ using 1:1:1 allocation ratio. After each SMC monthly distribution, children will be visited at home to confirm drug administration and followed-up for 1 year. Anthropometric indicators will be recorded at each visit and blood samples will be collected for microscopy slides, haemoglobin measurement, and spotted onto filter paper for further PCR analyses. The primary outcome measure is the incidence of malaria in each arm. Secondary outcome measures will include mid-upper arm circumference and weight gain from baseline measurements, coverage and compliance to SMC, occurrence of adverse events (AEs), and prevalence of molecular markers of antimalarial resistance comprising *Pfcrt*, *Pfmdr1*, *Pfdhfr,* and *Pfdhps*.

**Discussion:**

This study will demonstrate an integrated strategy of malaria and malnutrition programmes in order to mutualize resources for best impact. By relying on existing strategies, the policy implementation of this joint intervention will be scalable at country and regional levels.

**Trial registration:**

ClinicalTrials.gov NCT04238845. Registered on 23 January 2020

https://clinicaltrials.gov/ct2/show/NCT04238845

## Administrative information

The order of the items has been modified to group similar items (see http://www.equator-network.org/reporting-guidelines/spirit-2727-statement-defining-standard-protocol-items-for-clinical-trials/).

## Introduction

### Background and rationale {6a}

Malaria is hyper-endemic in Burkina Faso and many sub-Saharan African countries [1]. According to the National Malaria Control Program (NMCP) approximately 11,915,816 malaria cases and 4144 malaria-related deaths were reported in 2017 in Burkina Faso [2, 3]. Numerous malaria control interventions have been implemented in Burkina Faso in order to achieve the 2020 Sustainable Development Goal (SDG) 3 [4]. Seasonal malaria chemoprevention (SMC) ranks among the largest and reliable interventions for malaria control in countries with marked seasonality of malaria transmission. The goal of this intervention is to treat any existing infections and maintain protective drug concentrations in the blood throughout the complete high transmission season. This preventive measure involves administering antimalarial drugs (amodiaquine-sulfadoxine-pyrimethamine) to children aged 3–59 months on a monthly basis during the high transmission peak. SMC is recommended by the World Health Organization (WHO) and is known to reduce malaria morbidity by 30 to 83% [5–8]. In Burkina Faso, SMC is implemented from July/August to October/November each year. Despite the implementation of this strategy, the burden of malaria and associated mortality is still very high in this target population in Burkina Faso. This raises questions about other hidden factors that can negatively affect the effectiveness of SMC intervention.

At the same time, malnutrition is a major cause of childhood morbidity and mortality in low- and middle-income countries such as Burkina Faso [9, 10]. Malnutrition can lower immune system leading to increased susceptibility to malaria in the population. The Nutrition Direction, which is the agency established to address malnutrition problems in Burkina Faso, currently aims to scale-up Community Management of Acute Malnutrition (CMAM) [11, 12]. This approach involves timely detection of severe acute malnutrition in the community and provision of treatment for those without medical complications with ready-to-use therapeutic foods or other nutrient-dense foods at home. Both malaria and malnutrition are highly prevalent in rural settings. Furthermore, malaria seasonal peak coincides with period of food crisis in the country (as it is the farming period) suggesting that malnutrition may influence malaria incidence during that period. Children under 5 years again represent the most vulnerable group. Importantly, treating micronutrient deficiencies is known to reduce malaria morbidity and mortality [13, 14]. Plumpy’Doz™ is specifically formulated for the prevention of malnutrition in children from 6 months of age and adults [15, 16]. Evidence also shows that vitamin A-zinc supplementation reduce malaria morbidity [13]. A reduction by 20–30% of malaria incidence through micronutrient supplementation such as vitamin A-zinc has also been reported [13, 14].

These aspects underlie the idea of the proposed SMC-NUT project. This combined strategy could reduce the burden of malnutrition, enhance the immune system, and therefore decrease the susceptibility and severity of malaria in children under SMC coverage. This project will serve as pilot study for integrated strategy in order to mutualize resources for better impact. By relying on existing strategies, the policy implementation of this joint intervention will be scalable at country and regional levels.

### Objectives {7}

The overarching aim of the study is to study the impact of nutritional supplementation on different malaria indicators. The primary objectives include (i) assessing in a randomized open-label trial whether SMC + vitamin A + zinc or SMC + vitamin A + Plumpy’Doz™ is more effective and safe in reducing uncomplicated malaria incidence, severe malaria incidence, and related mortality compared to the SMC + vitamin A alone and (ii) to investigate the impact of the combined strategy in reducing the burden of malnutrition through reduction of anaemia incidence, mid-upper arm circumference, and weight gain.

Secondary objectives include (i) to assess the impact of each treatment arm on the circulating parasite population through monitoring the temporal trend of antimalarial resistance molecular markers *pfcrt*, *pfmdr1*, *dhfr,* and *dhps*; (ii) to assess the coverage and compliance to SMC in the study area; and (iii) to quantify the overall occurrence of adverse events (AEs).

### Trial design {8}

This will be a randomized open-label trial. Children (6–59 months) under SMC coverage receiving vitamin A supplementation will be randomly assigned to one of the three study arms (a) SMC + vitamin A alone, (b) SMC + vitamin A + zinc, or (c) SMC + vitamin A + Plumpy’Doz™ using 1:1:1 allocation ratio.

## Methods: Participants, interventions, and outcomes

### Study setting {9}

The study will take place in Nanoro, a regional direction of the Institut de Recherche en Sciences de la Santé (IRSS) in Burkina Faso. Nanoro is a rural area situated in the central part of Burkina Faso, around 85 km from Ouagadougou, the capital city of Burkina Faso. Data will be collected in four villages (Soaw, Rakalo, Zoetgomdé, and Kalwaka) covered by two peripheral health facilities (Soaw and Zoetgomdé). Malaria is hyper-endemic in Nanoro with a marked seasonality of transmission making it an ideal place for studying the impact of SMC intervention [17, 18]. Through its Health and Demographic Surveillance System (HDSS) platform, Nanoro offers an ideal opportunity to conduct such a study requiring a long-term follow-up period [19].

### Eligibility criteria {10}

Children will be included in the study if they fully comply with the following criteria: (i) children under both interventions coverage (SMC, vitamin A supplementation), i.e. 6–59 months old; (ii) resident within HDSS coverage area; (iii) ability to complete the study follow-up period; and (iv) written consent obtained from parents. Exclusion criteria are (i) individual not under both interventions coverage, (ii) children under both interventions coverage who did not receive any of the treatment (amodiaquine-sulfadoxine-pyrimethamine or vitamin A), (iii) ill individual at the time of the enrolment including uncomplicated/severe malaria or severe malnutrition, (iv) known allergy to vitamin A or zinc or Plumpy’Doz™, (v) planned travel or inability to complete the study follow-up, and (vi) unwillingness to participate to the study.

### Who will take informed consent? {26a}

Before starting the study, the community will be informed on the purpose of the study through the community leaders and a general consent will be obtained. A written informed consent will be obtained from all the study participants before enrolment. Parent/guardians of eligible children will receive in advance a copy of the study information sheet and the consent form from community health workers which they are welcome to discuss with their family members and friends. The information sheet will describe relevant information related to the study such as the purpose of the study, the study procedures, the confidentiality of recorded data, and the risks and benefits of the participation.

As the study involves minors (children aged 6–59 months), the parents or guardians will be asked to sign the consent to participate in the study.

If a parent or guardian is unable to read or write, a signature from an impartial adult witness present during the informed consent discussion and a thumb print of the parent/guardian will be obtained. The impartial witness will ensure that the reading of the consent form to the potential participant has been performed accurately, and the parent/guardian has had the opportunity to ask questions and therefore confirm that the parent/guardian has given consent freely.

### Additional consent provisions for collection and use of participant data and biological specimens {26b}

In the inform consent procedure, parent/guardians will be asked about future investigations on the unused blood samples. They will be explained that future investigations will only focus on the understanding of the parasite resistance mechanisms. No genetic testing about human host will be performed.

### Interventions

#### Explanation for the choice of comparators {6b}

Seasonal malaria chemoprevention (SMC) is one of the routine malaria control intervention and all children from 3 to 59 months old in the country are expected to be covered. In addition, vitamin A supplementation campaign is part of the national strategy for prevention of malnutrition in children (6–59 months) in Burkina Faso. The comparator represents children receiving both interventions as part of routine strategy for preventing malaria and malnutrition in Burkina Faso.

#### Intervention description {11a}

All interventions will be implemented in strict compliance with preventive measures against the spread of COVID-19 disease such as wearing masks and the use of hydroalcoholic gel. Prior to SMC first round, the targeted population living across HDSS area will be identified from the dataset of the last update round (sampling frame). Potential study participants will be randomly drawn from this sampling frame (Fig. 1).

**Fig. 1 Fig1:**
[figure not shown]
Study flowchart diagram

Home visit will be performed to confirm the presence of the child, notify, and inform parents of eligible participants about the study and where possible a written informed consent will be obtained. Absent children or children whose parents are not willing to participate will not be considered and will be replaced by other eligible children from the list.

##### SMC intervention

The SMC intervention is based on a complete dose administration of amodiaquine-sulfadoxine-pyrimethamine and will be implemented nationally by the NMCP. According to the national malaria cases management guidelines, amodiaquine-sulfadoxine-pyrimethamine (AQSP) will be administered once daily over 3 days [2]. The first dose will be administered under observation by the community health workers (CHW), while the remaining doses will be taken unobserved during the following 2 days.

##### Vitamin A supplementation

Similarly, vitamin A supplementation will be organized by the Nutrition Direction. Vitamin A will be administered as single dose of 200,000 UI per child under supervision by the CHW. All these interventions (SMC and vitamin A supplementation) will be implemented through the operational entity of the Ministry of Health in the study area which is the health district of Nanoro.

##### Plumpy’Doz™ supplementation

Plumpy’Doz™ is a ready-to-use nutritional lipid-based nutrient supplement that can be used at home without prior preparation. However, parents/guardians will be advised about the mode of administration of the product, with special interest paid to hygiene precautions. Each child will receive 1 sachet/day for 4 months (SMC period).

##### Zinc supplementation

Zinc supplementation (the equivalent of 10 mg of elemental zinc) will be provided on a daily basis during 6 days per week for 4 months (SMC period).

#### Criteria for discontinuing or modifying allocated interventions {11b}

It is anticipated that all of the product will be well tolerated. However, an efficient pharmacovigilance system will be put in place to ensure prompt reporting and management of adverse events requiring medical care and supplementation will be interrupted in case of frequent occurrence of related serious adverse events.

#### Strategies to improve adherence to interventions {11c}

All the products that will be used in this study are already used as part of routine management and prevention of malnutrition. Before enrolment and at each visit, we will insist on communication/sensitization about special care requirements for investigational product.

#### Relevant concomitant care permitted or prohibited during the trial {11d}

No concomitant care and routine interventions are prohibited during the trial. However, all concomitant care and interventions during the trials will be recorded.

#### Provisions for post-trial care {30}

There is no anticipated harm and compensation for trial participation and no anticipated provision for post-trial care.

#### Outcomes {12}

Primary outcomes include (i) the relative incidence of clinical malaria, severe malaria, and anaemia in SMC + vitamin A group (control group) compared to each of the two intervention arms, i.e. SMC + vitamin A + supplement and (ii) the mid-upper arm circumference gain and weight gain from the enrolment to the end of the 12-month study period in the intervention groups compared to the control group. Secondary outcomes include (i) the prevalence of mutant alleles of *pfcrt, pfmdr1, pfdhfr*, and *pfdhps* from the enrolment to the end of the 6-month study period in malaria-positive sample and (ii) SMC coverage in the area which will be determined as the ratio of children who actually received the intervention to the predetermined sample of eligible children from the HDSS dataset. (iii) Compliance will be determined by calculating, for each participant, the ratio between the number of tablets/packets taken and the number of tablets/packets that the patient should have taken. Two groups of participants will be described: compliant = 100% treatment compliance and non-compliant = other cases, and (iv) the incidence of adverse events in each study arms.

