#### Sample size {14}

Sample size calculation was carried out with incidence of malaria as the primary outcome measure under the assumption that the expected proportion of children 6–59 months who will acquire malaria in the absence of seasonal malaria chemoprevention (SMC) during the rainy season in Burkina Faso is 50%. The introduction of SMC is expected to reduce this proportion to 30%. The SMC programme together with nutritional intervention is expected to reduce this to 20%. The aim is to demonstrate that SMC + nutritional supplement arm is superior to the SMC alone arm in reducing the incidence of malaria. On this basis, a one-side α of 0.025 was chosen. Type II error was controlled at 20% (i.e. β = 0.20 or 80% power). Based on these parameters, a sample size of 294 was required for each pair-wise comparison (SMC + vitamin A vs SMC + vitamin A + zinc, and SMC + vitamin A vs SMC + vitamin A + Plumpy’Doz™). Hence, an overall sample size for the study was estimated at 882 (3 × 294) to detect a 10% difference in risk of malaria occurrence between SMC alone group and any of SMC + supplement group. Further assuming that 20% of the individuals will be lost to follow-up, an adjusted sample size of 353 children per arm was required. The final estimated sample size for this study is thus 1059 children.

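### The protocol names one primary outcome in two places and five or six in two others, and its sample size covers only malaria incidence, per comparison, at unadjusted alpha

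*Protocol article*

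**What the plan says.** Four places in the protocol article define what is primary.

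- **Abstract, Methods:** "The primary outcome measure is the incidence of malaria in each arm". The next sentence begins "Secondary outcome measures will include mid-upper arm circumference and weight gain from baseline measurements".
- **Sample size {14}:** "Sample size calculation was carried out with incidence of malaria as the primary outcome measure". It assumes 30% with malaria in the control arm and 20% with a supplement, one-sided alpha 0.025 and 80% power. This gives 294 per arm for each pairwise comparison, "to detect a 10% difference in risk of malaria occurrence between SMC alone group and any of SMC + supplement group".
- **Outcomes {12}:** "Primary outcomes include (i) the relative incidence of clinical malaria, severe malaria, and anaemia in SMC + vitamin A group (control group") set against each of the two supplement arms, and, also as primary, "the mid-upper arm circumference gain and weight gain from the enrolment to the end of the 12-month study period".
- **Objectives {7}:** the first primary objective covers "uncomplicated malaria incidence, severe malaria incidence, and related mortality compared to the SMC + vitamin A alone". The second covers anaemia, MUAC and weight gain.

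Statistical methods {20a} leaves the analysis methods to a statistical analysis plan. That plan may be revised during the study and is to be final before database lock. It is not at hand.

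**The concern.** MUAC gain and weight gain cannot be both primary and secondary. Suppose malaria incidence shows no difference and one supplement arm gains more weight than control. Under Outcomes {12} that is a positive result on a primary outcome. Under the Abstract it is a secondary observation in a trial whose primary result is null.

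Timing makes this worse. The trial is open-label, and the analysis plan can change until shortly before database lock. If the protocol does not settle the primary set, it could be settled after outcomes by arm have become visible.

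The design supports only one of these readings. The sample size is worked out for malaria incidence alone. It makes no allowance for a second comparison against the same control, nor for further primary outcomes.

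**Working it through.** **1. The four definitions side by side**

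| Outcome | Abstract | Sample size {14} | Outcomes {12} | Objectives {7} |
|---|---|---|---|---|
| Malaria incidence | primary | primary | primary (as clinical malaria) | primary (as uncomplicated malaria) |
| Severe malaria | not listed | – | primary | primary |
| Anaemia | not listed | – | primary | primary |
| MUAC gain | secondary | – | primary | primary |
| Weight gain | secondary | – | primary | primary |
| Malaria-related mortality | not listed | – | not listed | primary |

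The MUAC and weight rows contradict each other outright. The mortality row is a primary objective with no matching outcome. Five outcomes times two comparisons gives ten primary comparisons under Outcomes {12}.

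**2. Reproducing 294 per arm**

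Inputs from Sample size {14}: p1 = 0.30, p2 = 0.20, one-sided alpha 0.025 (z = 1.960), power 0.80 (z = 0.842). With pooled variance, no continuity correction and a mean proportion of 0.25:

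n = [1.960 × √(2 × 0.25 × 0.75) + 0.842 × √(0.30 × 0.70 + 0.20 × 0.80)]² / 0.10²
= [1.2002 + 0.5119]² / 0.01 = 293.2, rounded up to **294**.

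The stated figure is reproduced exactly. With alpha split to 0.0125 (z = 2.241), n = [1.3726 + 0.5119]² / 0.01 = 355.1, rounded up to 356. So 294 spends the full 0.025 on each comparison.

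**3. Error over the two malaria comparisons**

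If independent: 1 − 0.975² = 4.9%. With equal arms and a shared control, the two test statistics correlate at 0.5, and simulation gives about **4.5%**.

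**4. Error over ten comparisons, if all used one-sided 0.025**

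The protocol does not state this level for the other outcomes, so these figures are conditional. If independent: 1 − 0.975¹⁰ = 22.4%. By simulation with the shared control:

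| Assumed correlation between outcomes | Chance of at least one false positive |
|---|---|
| 0 | 20.7% |
| 0.3 | 18.0% |
| 0.6 | 14.2% |

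**5. Power per malaria comparison**

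Power = Φ[(0.10 × √n − c × 0.6124) / 0.6083], where c is the critical value. The planned loss leaves 353 × 0.8 = 282.4, about 282 per arm.

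| Test | c | n = 294 | n = 282 |
|---|---|---|---|
| Unadjusted 0.025 | 1.960 | 80.1% | 78.5% |
| Dunnett, two comparisons | 2.212 | 72.3% | 70.3% |
| 0.0125 (first Holm step) | 2.241 | 71.3% | 69.3% |

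**The case against.** Several stronger readings are tempting, and the document does not support them.

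- **Ten primary tests at one-sided 0.025.** That level appears only in Sample size {14}, for the two malaria comparisons. No level is given for severe malaria, anaemia, MUAC or weight gain. The 14–22% range shows what would follow from using 0.025 throughout; it is not a property of the stated plan.
- **No control of multiplicity.** The article states none, but it defers methods to an analysis plan that may contain it. Its absence here is not a fault.
- **Success if any supplement arm wins.** The wording about any supplement group describes the difference to be detected, and the same paragraph speaks of each pairwise comparison. No success rule is stated. Whether two different supplements against one control need joint adjustment is a debatable design choice.
- **A handful of deaths reported as a primary result.** Background {6a} cites "approximately 11,915,816 malaria cases and 4144 malaria-related deaths were reported in 2017 in Burkina Faso", which is 0.035% deaths per case. At an assumed 0.3 cases per child, that is 1059 × 0.3 × 0.000348 = 0.11 expected deaths, and about 1.1 at ten times as many cases. The ratio is national and not specific to this age group or site, so it is only a rough guide, and it does not point to a handful. The sounder point is that mortality is a primary objective with no matching outcome.

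It is also fair to say that Objectives {7} and Outcomes {12} agree on treating the nutritional outcomes as primary, and that the Discussion gives malnutrition much weight. Amending the Abstract would be another way to reconcile the text. It would leave several primary outcomes in a trial sized for one.

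None of this removes the contradiction. The deferral covers analysis methods, analysis populations and missing data. It does not cover which outcome is primary, which the protocol fixes in incompatible ways.

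**Conclusion.** The contradiction stands on the protocol's own text and does not depend on the unseen analysis plan. It can change what the trial is able to conclude, so it should be resolved before database lock.

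The sample size is arithmetically what it claims to be: 80% power for malaria incidence, for one comparison at a time, at unadjusted one-sided 0.025. It offers no stated support for any other primary outcome. If the two malaria comparisons count as one family, the familywise error is about 4.5% rather than 2.5%. Controlling it would bring per-comparison power to 71–72% with 294 analysed per arm, or 69–70% with about 282. Those powers rest on the protocol's 30% and 20%, equal arms and a pooled-variance test. The ten-comparison figures rest in addition on a common level and on assumed outcome correlations, neither of which the document gives.

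**What to change.** 1. Before database lock, align the Abstract, Objectives {7}, Outcomes {12} and Sample size {14} on one primary outcome set. The simplest choice is malaria incidence as sole primary, because it is the only outcome the trial is sized for. Anaemia, MUAC gain and weight gain would then be secondary, and severe malaria and mortality secondary or descriptive. Use one term for the primary outcome throughout, since the sections variously say malaria, clinical malaria and uncomplicated malaria.
2. If more than one outcome stays primary, state a testing hierarchy or an alpha split.
3. In Sample size {14}, say that the 80% power is per comparison, for malaria incidence only, at unadjusted one-sided 0.025.
4. State whether the two supplement arms form one family. If they do, name the procedure (Dunnett or Holm) and restate the per-comparison power as in the verdict.

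The cost is a protocol amendment, reported to the ethics committee and the regulator as the protocol requires, in a trial that has already started recruiting. If the arms are tested as one family, the stated power also becomes about 8–9 points less favourable at 294 analysed per arm, and about 10–11 points below the stated 80% once the planned loss is counted. No new data are needed.
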